### Definitions

Early group: patients receiving botulinum toxin type A (BOTOX) injection immediately after randomization.

Late group: patients receiving placebo injection immediately after randomization and receive BOTOX injection 2 weeks after randomization if the FOIS score < 3.

Retreat group: patients within the “early group” with a score < 3 of FOIS 2 weeks after BOTOX injection and will receive another BOTOX injection.

Figure 1 is a graphical representation of the study design.

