### Sample size estimates

To detect significant differences between groups using an independent sample *t* test, a sample size of 44 patients is needed, assuming a spontaneous recovery mean ± SD in the late group of 2.6 ± 1.1 [29, 30], and a recovery mean ± SD of 4 ± 1.8 in the early group, as determined by our pilot study. These estimates assume a type I error of 0.05, a power of 0.80, and an estimated 10% rate of loss to follow-up.

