### Statistical analyses

The statistical analysis will be performed using the Statistical Package for Social Sciences (SPSS) version 23.0 for Windows by a statistician who is not involved in the study. A chi-square test will be used to compare the expulsion rate between the early and late groups. If the expulsion rate of the two groups is not statistically significant (*p* > 0.05), compliance of the groups will be considered similar. On the contrary, it is considered that the compliance of the two groups of patients is inconsistent, and it is necessary to re-recruit research cases, which will be assessed by the Data Monitoring Committee. Normally distributed data will be presented as the mean ± standard deviation. Categorical data will be presented as the frequency and proportions. Assumptions of normality will be tested with the Kolmogorov-Smirnov test. The parametric data will be analyzed by the independent sample *t* test, while the non-parametric data will be analyzed by the rank sum test. The *p* values ≤ 0.05 will be considered statistically significant. A comparison between two groups will be used to assess whether the efficacy (represented by FOIS, UES residual pressure, UES resting pressure, duration of UES relaxation, etc.) is different. A chi-square test will be used to compare the differences in the proportion of patients with improved swallowing function (assessed by FOIS) between the groups. Improvement prior to and post treatment in both groups will be assessed. Efficacy evaluation indicators (FOIS, UES residual pressure, UES resting pressure, duration of UES relaxation, etc.) will be compared two weeks after the first and second injections to assess improvement in the groups. A logistic regression method will be used to establish a probability model of BTX efficacy and influencing factors. The effect of each influencing factor on BTX efficacy (OR and 95% confidence interval) will be quantitatively analyzed to determine the interpretable accuracy and reliability of the coefficient *R*^2^ evaluation of the established efficacy and influencing factors model, with the FOIS score of the BTX group will be defined into effective and non-effective, a two-category variable *Y* (FOIS ≥ 3, *Y* = 1; FOIS<3, *Y* = 0). Patients’ age, gender, stroke lesion location, UES residual pressure, UES resting pressure, duration of UES relaxation, velopharyngeal peak pressure and hypopharyngeal peak pressure, UES opening, pharyngeal construction ratio, residue of bolus in the epiglottis valley or piriform sinus, penetration, and aspiration will be used as influencing factors of variable Xi (*i* = 1, 2, …11). A chi-square test will be used to compare the incidence of adverse events between the groups. An interim analysis will be performed after inclusion of the first 22 patients by a statistician who is not involved in this research. The data collection of the study will be assessed and confirmed by the Data Monitoring Committee, which can make decision to stop the research when it is harmful or futile.

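### The BTX efficacy factor model leaves out starting FOIS although success is a fixed cut at FOIS 3, so listed severity factors may partly reflect where the patient started

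*Protocol article*

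**What the plan says.** The Statistical analyses section of the protocol article describes a logistic regression in which "the FOIS score of the BTX group will be defined into effective and non-effective, a two-category variable". A FOIS of 3 or more is success and a lower score is failure. The factors begin with "age, gender, stroke lesion location, UES residual pressure, UES resting pressure, duration of UES relaxation", continue with the pharyngeal peak pressures, UES opening and the pharyngeal ratio, and end with "residue of bolus in the epiglottis valley or piriform sinus, penetration, and aspiration will be used as influencing factors of variable Xi", indexed from 1 to 11. FOIS before treatment is not named. The odds ratios with 95% intervals are to be read as the effect of each factor on BTX efficacy.

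The Inclusion criteria require a FOIS of at most 2. Under Definitions, late-group patients "receive BOTOX injection 2 weeks after randomization if the FOIS score < 3". The retreat group consists of "patients within the “early group” with a score < 3 of FOIS 2 weeks after BOTOX injection". So everyone given BTX starts below the success cut.

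**The concern.** The cut is absolute but the starting point is not the same for everyone. If the scale starts at 1 (the article does not give its lower end), a patient at level 2 needs a gain of one level to count as a success and a patient at level 1 needs two. Where the patient started is therefore likely to predict success, whatever BTX does.

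Several listed factors describe the severity of the same swallowing disorder. If one of them goes with starting FOIS, its odds ratio takes up part of the starting-level effect. A reader could then take it as a marker of who responds to BTX when it partly marks who was closer to the cut. The outcome, the cut and a numbered factor list are all fixed in the article, so this concerns a stated rule and not a detail left open.

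**Working it through.** **The plan's own figure.** The sample size inputs are "assuming a spontaneous recovery mean ± SD in the late group of 2.6 ± 1.1" and "a recovery mean ± SD of 4 ± 1.8 in the early group". The averaged SD is √((1.1² + 1.8²)/2) = 1.492 and the difference is 4 − 2.6 = 1.4. With two-sided α 0.05 and power 0.80, n = 2 × 7.849 × 2.225 / 1.96 = 17.8, so 18 per arm. The noncentral t gives 19 per arm (power 0.804). Then 19/0.9 = 21.1, so 22 per arm and 44 in total. The stated 44 reproduces and is not in dispute.

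**Inputs for the size of the problem.**
- From the article: later FOIS on BTX 4 ± 1.8; entry FOIS at most 2.
- Assumed: a roughly normal later score with the cut at 2.5; starting levels 1 or 2, with a share f = 30% to 70% at level 2; a one-level higher start raises the later score by s = 0.5 to 1.0; a binary factor with no effect of its own, whose two categories differ by 30 to 50 percentage points in the share starting at level 2.

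**Step 1, effect of starting level.** The mean later score is 4 − s·f from level 1 and 4 + s·(1 − f) from level 2. The residual SD is √(1.8² − s²·f·(1 − f)).

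Example with s = 1, f = 0.5: means 3.5 and 4.5; residual SD √(3.24 − 0.25) = 1.73; P(FOIS ≥ 3) = 0.718 and 0.876; odds ratio (0.876/0.124)/(0.718/0.282) = 2.78 before rounding.

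Over the whole range, P(success) is 0.68 to 0.78 from level 1 and 0.82 to 0.90 from level 2, with an odds ratio of about 1.6 to 2.8.

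**Step 2, spurious odds ratio for a null factor, unadjusted.** Same example, with 75% against 25% starting at level 2:
- 0.75 × 0.876 + 0.25 × 0.718 = 0.837
- 0.25 × 0.876 + 0.75 × 0.718 = 0.758
- odds ratio 1.64

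| Rise per starting level | Spurious odds ratio, single factor |
|---|---|
| 0.5 | about 1.15 to 1.3 |
| 1.0 | about 1.3 to 1.7 |

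A second calculation fixed overall success at 76% (the mean success rate quoted in the Background) and set the starting-level odds ratio at 2, 4 or 8. It gave 1.15, 1.30, 1.43 for shares of 40% against 60%, and 1.31, 1.69, 2.07 for 30% against 70%. If the factor is unrelated to starting FOIS, the result is 1.0.

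**Step 3, several severity factors together.** I simulated a very large sample with four null binary factors, linked to one another only through starting FOIS (f = 0.5). Entered jointly, each showed about 1.1 to 1.2 for a rise of 0.5 and about 1.25 to 1.35 for a rise of 1.0. Another check, with correlated severity factors, gave about 1.1 to 1.2. Replacing one of the four by starting FOIS brought the others back to about 1.0.

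**Step 4, how often it would show.** With 22 BTX patients and the 76% assumption, a null factor tested alone reaches p ≤ 0.05 in about 5% to 11% of trials for the 40/60 and 30/70 splits, and 7% to 18% for a 20/80 split. The nominal rate is 5%.

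**Step 5, capacity of the model.** At 76% success, 22 patients give 22 × 0.24 = 5.3 non-responders, or 5.3/11 = 0.48 per term. In simulations with independent factors, 11 terms on 22 patients had no finite estimate in about 89% of runs. With all 44 patients contributing, this fell to about 4%.

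**The case against.** **The harm is not certain.** A reader might infer that factors tied to a better start will be reported as determinants of efficacy. The documents do not support that. It needs a listed factor clearly related to starting FOIS and a material effect of starting FOIS, and the article gives a figure for neither. With 22 patients such a factor would seldom reach significance. This stands, and the point is worded as what may happen.

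**The design limits the spread.** Nobody starts as a success, so a coded success always means a gain of at least one level. That is right, but it does not equalise the required gain between patients starting at different levels. If nearly all entrants sit at one level, the point largely disappears.

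**The single-factor figures are not the planned model.** The listed measures may absorb part of each other's share when entered together. This stands; step 3 shows smaller values, though not 1.0.

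**Leaving FOIS out may be deliberate.** Poor UES opening or residue may cause a low FOIS, and conditioning on FOIS could remove part of their genuine contribution. This is a fair point about interpretation. It is a reason to say what each odds ratio is conditional on. Without the starting score, predicting the level reached cannot be told apart from predicting response.

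**The model has a larger weakness.** Too few non-responders for 11 terms matters more than a modest bias, and adding starting FOIS does not cure it. This also stands.

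**Conclusion.** The point holds as a minor improvement to an exploratory model. The article fixes an absolute success cut and a factor list without starting FOIS, and entry allows more than one starting level if the scale starts at 1. The odds ratios may therefore mix response to BTX with distance from the cut. The likely size is a spurious odds ratio of about 1.15 to 1.7 for one unadjusted factor, and less with the severity measures entered jointly. This rests on the assumed starting distribution, slope and imbalance, and on the factors being measured before treatment, which the article does not state.

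A reader might also infer that the randomised FOIS comparison is biased. It is not: allocation is random, and this model uses BTX-treated patients only.

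**What to change.** Enter FOIS measured immediately before the BTX injection being modelled as the first term. That is the screening value for the early group's first injection and the 2-week value for late-group or repeat injections. Put it in place of one overlapping severity measure, for example residue or the penetration and aspiration item, so that the number of terms does not grow. Report each factor's odds ratio as conditional on this score and label the model exploratory.

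The cost is a line or two of wording and one listed factor dropped. No new data are needed: entry and the decision on a later BTX injection both already depend on FOIS. The shortage of non-responders per term remains and needs its own remedy.

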## Background

Functional swallowing occurs due to a series of well-coordinated movements that allow transport of food bolus from the oral cavity into the stomach while avoiding passage of food bolus into the airway [1]. Dysphagia occurs due to neurological disorders that impair the transport of food from the oral cavity to the stomach efficiently and/or safely [2] and is associated with an increased risk of pulmonary complications, dehydration, malnutrition, and mortality [1, 3]. Dysphagia is a common complication in stroke patients with a morbidity rate between 20 and 90%, depending on the assessment methods [4].

The upper esophageal sphincter (UES) is the high-pressure physical barrier to the transport of a food bolus or liquids between the pharynx and esophagus. The cricopharyngeal muscle is main muscle responsible for UES function [5]. This muscle remains in a contracted position during respiration, preventing air from entering into the esophagus and relaxes and opens during swallowing or vomiting [2]. Cricopharyngeal dysfunction (CPD), characterized by difficulty of food bolus entering the esophagus, occurs often due to 3 main factors: cricopharyngeal muscle spasm, incomplete laryngeal movement, and insufficient descending pressure of the bolus [2].

Cricopharyngeal achalasia is one of the main manifestations of CPD characterized by an uncoordinated state of relaxation or spasm of the cricopharyngeal muscle. Primary cricopharyngeal achalasia is a rare, idiopathic disorder [6]. Secondary cricopharyngeal achalasia occurs in various disorders, including stroke, Parkinson’s disease, and head and neck cancers [7]. Cricopharyngeal achalasia is one of the main causes of dysphagia after stroke [8]. Many swallowing problems recover spontaneously within 7 days after stroke, but approximately 8 to 50% of patients experience persistent difficulties in swallowing 6 months after stroke [9, 10]. The prevalence rates of dysphagia vary due to differences in the definition of dysphagia, method of assessing swallowing function, timing of swallowing assessment after stroke, and number and type of patients with stroke studied [11]. Early therapy for dysphagia is effective and can reduce serious complications [12]. For patients with persistent dysphagia, more effective treatments are needed to reduce morbidity and mortality.

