### Inclusion criteria

Patients are eligible for study participation if they fulfill all of the following criteria:
Meet the diagnostic criteria for stroke, listed in the *Diagnostic criteria of cerebrovascular disease in China (version 2019)* [24].Stable vital signs without severe cardiopulmonary diseaseAged 18–90 yearsFailed in swallowing function improvement after 1 week of balloon dilationFunctional Oral Intake Scale (FOIS) Score ≤ 2Cricopharyngeal muscle cannot completely open, verified by video fluoroscopic swallowing study (VFSS); moderate-severe residue in epiglottic valley or piriform sinus, evaluated by flexible endoscopic evaluation of swallowing (FEES).UES residual pressure > 20 mmHg by high-resolution manometry (HRM).Cooperation with treatment without dysfunction of hearing and comprehension.Provide informed consent on their own behalf (or by legally appointed representatives/authorities).

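### Time since stroke is used neither in the FOIS comparison nor in the BTX efficacy model: a cheap gain in precision is missed, and the BTX-only model cannot separate natural recovery from response

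*Protocol article*

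**What the plan says.** All places are in the protocol article.

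- **Background.** Recovery is tied to time: "Many swallowing problems recover spontaneously within 7 days after stroke", while roughly 8 to 50% of patients still have difficulties at 6 months. Among the reasons why reported dysphagia rates differ, the section lists "timing of swallowing assessment after stroke".
- **Inclusion and exclusion criteria.** Stroke enters as "Meet the diagnostic criteria for stroke", with no minimum or maximum time since onset. The only time element is one week of balloon dilation without improvement. Entry FOIS must be 2 or lower.
- **Sample size estimates.** The control-arm figure is named as natural recovery: "assuming a spontaneous recovery mean ± SD in the late group of 2.6 ± 1.1". The BTX arm is planned at "a recovery mean ± SD of 4 ± 1.8 in the early group".
- **Allocation and randomization.** One random list of 44, 1:1; no stratification is described.
- **Statistical analyses.** FOIS is compared by an independent t test or a rank sum test. A logistic model of BTX efficacy takes the BTX group only, with FOIS of 3 or more as success. Its eleven indexed factors are named. They include "age, gender, stroke lesion location, UES residual pressure, UES resting pressure, duration of UES relaxation" and further manometric, fluoroscopic and endoscopic measures, but not time since stroke.

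**The concern.** The plan expects control patients to improve unaided: they enter at FOIS 2 or lower and are assumed to average 2.6. It also describes recovery as dependent on time after stroke. A patient a few weeks after stroke and one many months after can both enter, and their chances of improving without BTX over two weeks may differ. A baseline variable with that potential is left out of both stated analyses.

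The consequences differ between the two.

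- **FOIS comparison.** Randomisation protects it. Variation in stroke age goes into the residual error, and adjustment could remove part of it.
- **Efficacy model.** Randomisation gives no protection, because no control patients are in the model. A patient who would have reached FOIS 3 anyway counts as a BTX responder. Any listed factor that correlates with stroke age can then appear, with an odds ratio and interval, as a determinant of BTX efficacy.

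**Working it through.** **Inputs from Sample size estimates.** Means 2.6 and 4 (difference 1.4), SDs 1.1 and 1.8, type I error 0.05 (two-sided assumed, as sidedness is not stated), and "a power of 0.80, and an estimated 10% rate of loss to follow-up".

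**Step 1: the plan's own figure.** Pooled SD = √((1.1² + 1.8²)/2) = √((1.21 + 3.24)/2) = √2.225 = 1.492. By the noncentral t distribution, 18 per arm gives power 0.781 and 19 per arm gives 0.804, so 19 per arm are needed. Allowing for 10% loss, 19/0.9 = 21.1, rounded up to 22 per arm, 44 in total. The stated size is reproduced.

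**Step 2: precision without adjustment.** With 10% loss, 22 × 0.9 = 19.8, about 20 evaluable per arm. Standard error of the difference = 1.492 × √(2/20) = 0.472. Power is 0.82.

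**Step 3: precision with adjustment.** Let R² be the share of week-2 FOIS variance explained by log time since stroke. The documents do not give it, so 2% to 30% is assumed. Adjusted SD = 1.492 × √(1 − R²), with 37 degrees of freedom (40 patients less three coefficients):

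| R² (assumed) | Adjusted SD | Power, 20 per arm |
|---|---|---|
| 0 (unadjusted, 38 df) | 1.492 | 0.82 |
| 0.02 | 1.477 | 0.83 |
| 0.05 | 1.454 | 0.84 |
| 0.10 | 1.415 | 0.86 |
| 0.20 | 1.334 | 0.90 |
| 0.30 | 1.248 | 0.93 |

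Any further gain from baseline FOIS is not counted.

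**Step 4: chance imbalance in one trial.** The standardised difference in log time between arms has SD √(2/20) = 0.316 at 20 per arm, so a difference of 0.5 SD or more has probability about 0.11 (0.10 at 22 per arm). Such a difference moves the unadjusted FOIS difference by 0.5 × √R² × 1.492: 0.24, 0.33 and 0.41 points for R² = 0.1, 0.2 and 0.3. Divided by the standard error of 0.472, these are 0.50, 0.71 and 0.87 standard errors. This variation is already inside the t test's standard error and is not an extra error on top of it.

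**Step 5: the efficacy model.** No arithmetic is needed. Success is an after-treatment FOIS of 3 or more in BTX patients. The outcome therefore mixes natural recovery with response to BTX, and the model holds no untreated patients and no stroke-age term to separate them. If the BTX group means the early group, about 22 patients carry eleven indexed factors, so a new factor should replace another and not be added.

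**The case against.** The case on the other side is strong for the primary comparison.

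- **Bias.** A reader might infer that uncontrolled stroke age biases the BTX estimate. It does not: under 1:1 randomisation the unadjusted test is unbiased on average and keeps its type I error. Shifts of 0.24 to 0.41 points can be presented as 17% to 29% of the planned 1.4, but they are ordinary sampling error, each below one standard error. This stands.
- **Power.** A reader might infer that the trial is underpowered. The size of 44 is reproduced, and unadjusted power at 20 per arm exceeds 0.80. The planning SDs plausibly contain variation in stroke age already. This stands.
- **Strength of the link.** Nothing in the document fixes R². Entry selects a narrow group (low FOIS, raised UES residual pressure, incomplete opening, failed dilation), so a small R² is plausible. The failed-dilation rule removes much of the 7-day recovery window, and the remark on timing of assessment explains differences in prevalence, not individual prognosis. This stands as a limit on size. The expected spontaneous recovery in the control arm still comes from the plan itself.
- **Recording.** A reader might infer that the onset date is not collected. The list under Data collection and management names what is checked, and it also omits lesion location, which the efficacy model uses. The article does not show that the date is missing.
- **Left to an analysis plan.** Covariates often are. Here, however, the article names the test and enumerates the factors, so the point concerns stated choices.

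The objection does not reach the BTX-only model, although that model is secondary and does not carry the trial's main conclusion.

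**Conclusion.** The point holds as a worthwhile, low-cost improvement. It is not an error that invalidates the primary analysis. In the FOIS comparison the loss is of attainable precision: power 0.82 unadjusted against about 0.83 to 0.93 at 20 evaluable per arm. This rests on the planned means and SDs, a two-sided 0.05 level, and an assumed R² of 2% to 30%. At the low end the gain is negligible.

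The firmer part is the efficacy model. As specified, it cannot tell recovery that would have happened anyway from response to BTX, and its odds ratios should not be read as determinants of BTX efficacy. The size of that distortion cannot be derived from the document.

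**What to change.** 1. Make sure the stroke onset date is recorded for every patient, taken from hospital records for those already included.
2. Before unblinding, prespecify an ANCOVA of week-2 FOIS on treatment, log time from stroke to randomisation, and baseline FOIS. Keep the planned t or rank sum test as a supporting analysis.
3. Put time since stroke into the efficacy model in place of a lower-priority factor, chosen in advance, so that the model does not grow. Report that model as exploratory, and state that it describes outcome after BTX and not the effect of BTX.

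Entry criteria need not change; any time limit is for the investigators to decide.

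**Cost.** One date per patient and one or two degrees of freedom. The larger cost is a change of primary test: neither a t test nor a rank sum test takes a covariate. According to Trial status, 10 patients had completed the intervention at submission, so the change must be dated, justified and documented as made without sight of results by arm.

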**Methods:**

BECURE is a single-center randomized, placebo controlled, double-blinded, superiority clinical trial. To detect a significant difference between the 2 groups, a sample size of 44 patients is estimated. The intervention is BTX versus placebo, with 1:1 randomization. The randomization sequence from 1 to 44 was generated using the Statistical Package for Social Sciences. The study is divided into two phases. In the first phase, patients will be injected with BTX or the placebo. In the second phase, patients who received a placebo injection and those who did not respond to the first BTX injection will receive an injection of BTX. The primary outcome is the score of the Functional Oral Intake Scale (FOIS). The secondary outcomes are as follows: upper esophageal sphincter (UES) residual pressure, UES resting pressure, duration of UES relaxation, velopharyngeal and laryngopharyngeal peak pressure, UES opening, pharyngeal construction ratio, residue of bolus in the epiglottis valley or piriform sinus, and penetration and aspiration.

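### The logistic model of response in the BTX group lists 11 to 13 factors, too many for the number of BTX patients and expected non-responders

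*Protocol article*

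**What the plan says.** The Statistical analyses section of the protocol article states: "A logistic regression method will be used to establish a probability model of BTX efficacy and influencing factors". The outcome is binary (FOIS ≥ 3 or < 3) and the population is given in the phrase "with the FOIS score of the BTX group will be defined into effective and non-effective".

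The factors are age, gender, lesion location and the manometric, fluoroscopic and endoscopic measures. The list closes with "penetration, and aspiration will be used as influencing factors of variable Xi" and an index running from 1 to 11. That count holds only if the two peak pressures are one factor and penetration with aspiration is another. Counted singly there are 13, and lesion location or the four-level UES opening score could add further terms.

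The section promises an odds ratio and 95% CI for each factor, and an R-squared to judge the model's accuracy and reliability. It states no selection rule, penalty or cap on the number of factors.

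The sample size section covers only the t test on FOIS: "a sample size of 44 patients is needed". The abstract adds "The intervention is BTX versus placebo, with 1:1 randomization".

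**The concern.** A logistic model is limited by the smaller outcome class, here probably the non-responders. When factors are many relative to patients, some linear combination of them often splits responders from non-responders exactly, even if every factor is noise. This is separation. The likelihood then has no finite maximum, software prints very large odds ratios with meaningless intervals, and under complete separation R-squared climbs to its ceiling. The measure offered as evidence of accuracy would look best when the model has failed.

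The trial could then publish determinants of BTX response that are artefacts of fitting. The label is a second problem. A model fitted only to BTX-treated patients cannot tell factors that modify the effect of BTX from factors that predict recovery with or without it.

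**Working it through.** **Step 1: the plan's own figure.** The inputs from Sample size estimates are "assuming a spontaneous recovery mean ± SD in the late group of 2.6 ± 1.1", "a recovery mean ± SD of 4 ± 1.8 in the early group" and "a type I error of 0.05, a power of 0.80, and an estimated 10% rate of loss to follow-up". Two-sided alpha is assumed.
- Difference = 4 − 2.6 = 1.4. Common SD = √((1.1² + 1.8²)/2) = 1.49.
- The noncentral t distribution gives 19 per arm (power 0.804).
- 19/0.9 = 21.1, rounded up to 22 per arm, so 44 in total. The stated figure reproduces.

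**Step 2: patients in the model.** 44/2 = 22 in the BTX arm, and 22 × 0.9 = 19.8, about 20 evaluable.

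**Step 3: non-responders.** The protocol gives no count, so this is an assumption with two sources.
- Background, mean success rate 76%: 0.24 × 20 = 4.8, and 0.24 × 22 = 5.3.
- Planned FOIS 4 ± 1.8, normal approximation: Φ((2.5 − 4)/1.8) = 0.202 gives 4.0 of 20; Φ((3 − 4)/1.8) = 0.289 gives 5.8 of 20.

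The working range is therefore 4 to 6. Non-responders per factor: 4/11 = 0.36 to 6/11 = 0.55 with 11 factors, and 4/13 = 0.31 to 6/13 = 0.46 with 13.

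**Step 4: how often the model separates.** 1,000 data sets per setting, independent factors unrelated to outcome, either all continuous or four binary. Complete or quasi-complete separation was detected by linear programming. Ranges span the two factor types.

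| Patients | Non-responders | 11 factors | 13 factors |
|---|---|---|---|
| 20 | 4 | 98% | 99.9–100% |
| 20 | 5 | 94–95% | 99–100% |
| 20 | 6 | 91–92% | 98–99% |
| 20 | 10 | 78% | 95–96% |
| 22 | 4 | 96–97% | about 100% |
| 22 | 5 | 90–92% | 99% |
| 22 | 6 | 83–85% | 98% |
| 40 | 8 | 12–13% | 32–34% |
| 40 | 10 | 5–6% | 15–16% |
| 40 | 12 | 1–2% | 7–8% |

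Real effects raise these rates. With two factors shifted by 0.8 SD, 20 patients and 4 to 6 non-responders, separation with 11 factors is 96–99%.

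Closed-form check: for random outcome labels and 11 factors plus an intercept, Cover's counting formula gives P(Bin(n − 1, ½) ≤ 11). This is 82% at n = 20 and 67% at n = 22, averaged over all splits. It is in line with the simulated 78% at 10/10 and about 57–64% at 11/11.

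**Step 5: the wider reading.** The Definitions section gives late-group patients BTX at 2 weeks if FOIS < 3. From 2.6 ± 1.1, Φ((2.5 − 2.6)/1.1) = 0.46 and Φ((3 − 2.6)/1.1) = 0.64, so about 9 to 13 of 20. Pooling gives 29 to 33 patients, and at most about 40 if all evaluable late-group patients were injected.
- At 29 to 33 patients with 7 or 8 non-responders, separation is about 23–51% with 11 factors and 49–76% with 13. Non-responders per factor: 7/11 = 0.64 to 8/11 = 0.73.
- At 40 patients and 24% non-response, 9.6/11 = 0.87 per factor. At 28.9% it is 11.6/11 = 1.05.

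**Step 6: the label.** By the same approximation, 1 − 0.64 = 36% to 1 − 0.46 = 54% of the late group would reach FOIS ≥ 3 without BTX. Success in the BTX arm is therefore partly spontaneous recovery.

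**The case against.** The strongest objection is that the BTX group is not a defined term. The Definitions section names only early, late and retreat groups, and the Statistical analyses section also compares outcomes after the second injection. A model of BTX response might therefore pool late-group recipients. This stands. A reader might infer that the model will almost always separate and can carry no information at all. The documents support the first only for the randomised BTX arm, and on the pooled reading the second is too strong.

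Next, 4 to 6 non-responders is not a protocol figure. The 76% is a literature mean with a range of 43 to 100%, and the text does not say that success there meant FOIS ≥ 3. This stands as a caveat. It changes little at 20 patients, where separation is 78% even at an even split. At 22 patients an even split brings it down to about 57–64%.

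Third, joint entry of all factors is inferred, and selection rules are often left to an analysis plan that is not shown. This has some force, but the text commits the whole numbered list to one probability model with one R-squared.

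Finally, this is a secondary analysis. A reader might infer that the trial's main result is at risk. It is not: the FOIS comparison, the sample size and the safety comparison do not depend on this model.

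**Conclusion.** The point holds: the model has too many factors for its sample on either reading of the BTX group. For the randomised BTX arm with 4 to 6 non-responders, separation with 11 noise factors is 91–98% at 20 patients. At 22 it is 90–97% with 4 or 5 non-responders and 83–85% with 6. With 13 factors it is 98% or more throughout. On the pooled reading the failure is mainly overfitting: about one non-responder per factor at best, and under one at the 76% success rate.

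These figures assume independent factors, joint entry by ordinary maximum likelihood and the non-response rates in Step 3. The plan should be corrected here, but the defect is of secondary weight.

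**What to change.** In the Statistical analyses section:
- Remove the 11-factor model and the use of R-squared as evidence of accuracy and reliability.
- Define the BTX group: the arm randomised to BTX, or all BTX recipients with the time point for each.
- Report penalised odds ratios (for example Firth logistic regression) with 95% CIs, one factor at a time or with at most two pre-named factors per model, labelled exploratory. Other small-sample methods, such as ridge or exact logistic regression or a purely descriptive table, would also serve.
- Call the factors prognostic for reaching FOIS ≥ 3 among BTX-treated patients, not factors of BTX efficacy. A treatment-by-factor term in all 44 randomised patients would address effect modification in principle, but would be very imprecise at this size and is not needed for this correction.

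The cost is a change of analysis wording, with no effect on procedures, data collection or sample size. The downside is that no multivariable prediction model can be claimed, which these numbers would not support anyway.
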